## Abstract

**Background:**

Oesophageal cancer (EC) is the sixth leading cause of cancer death worldwide. Oesophageal resection is the only curative treatment option for EC which is frequently performed via an abdominal and right thoracic approach (Ivor-Lewis operation). This 2-cavity operation is associated with a high risk of major complications. To reduce postoperative morbidity, several minimally invasive techniques have been developed that can be broadly classified into either hybrid oesophagectomy (HYBRID-E) via laparoscopic/robotic abdominal and open thoracic surgery or total minimally invasive oesophagectomy (MIN-E). Both, HYBIRD-E and MIN-E, compare favourable to open oesophagectomy. However, there is still an evidence gap comparing HYBRID-E with MIN-E with regard to postoperative morbidity.

**Methods:**

The MICkey trial is a multicentre randomized controlled superiority trial with two parallel study groups. A total of 152 patients with oesophageal cancer scheduled for elective oesophagectomy will be randomly assigned 1:1 to the control group (HYBRID-E) or to the intervention group (MIN-E). The primary endpoint will be overall postoperative morbidity assessed via the comprehensive complication index (CCI) within 30 days after surgery. Specific perioperative parameters, as well as patient-reported and oncological outcomes, will be analysed as secondary outcomes.

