### Outcomes {12}

#### Primary outcome/endpoint and assessment of primary outcome

The primary endpoint is overall postoperative morbidity within 30 days postoperatively measured via the comprehensive complication index (CCI) [17, 18]. The CCI ranges from 0 to a maximum of 100; the index expresses the cumulative morbidity that the patient experiences. The CCI is based on the established Dindo-Clavien classification (DCC) [22, 23]. A complication is any deviation from the normal postoperative course. The score is validated for oesophageal surgery, and a difference of 10 is regarded as a clinically relevant difference [18]. An endpoint reflecting the entire spectrum of complications like the CCI is highly appropriate to compare two different strategies like in the MICkey trial. The score will be calculated comprising all complications within 30 days.

A list of oesophagectomy-specific complications will be provided for all trial centres to facilitate documentation and assessment of postoperative morbidity according to the Esophagectomy Complications Consensus Group (ECCG) and the Dindo-Clavien grading system (Supplement 2) [24].

As postoperative oesophagogastroduodenoscopies (EGD) are frequent after oesophagectomy and performed routinely in some centres, a purely diagnostic EGD showing no pathological finding does *not* constitute a complication in the MICkey trial. Only if an endoscopic intervention (e.g. EndoVAC placement) is performed or a pathologic finding is identified on EGD (e.g. anastomotic leakage defined as “a full thickness GI defect involving oesophagus, anastomosis, staple line, or conduit irrespective of presentation or method of identification”) does this constitute a complication in the MICkey trial.

In the Addendum to the ICH E9 guideline, the estimand framework is recommended as a clear and transparent definition of “what is to be estimated” (International Council for Harmonization, 2019). An estimand is defined through the treatment, the targeted population, the variable (i.e. the endpoint), a specification of how to handle intercurrent events (post-randomization events) and a population-level summary. In the following, the primary estimand corresponding to the primary objective is described.

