#### Safety measures

20.Rate of serious adverse events defined as postoperative complication Clavien-Dindo grades III–V within 90 days after surgical intervention.

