### Participant timeline {13}

**Table Tabb:** 

**Visit**	**V1**	**V2**	**V3**–**5**	**V6**	**V7**	**V8**	**V9/V10**
	Before surgery	Surgery (day 0)	POD 2 (+1) POD 4 (+1) POD 7 (+2)	Discharge	POD 30 (±5)	POD 90 (±5)	12 months postop. 24 months postop.
	**Outpatient/inpatient**	**Inpatient**			**Outpatient**	**Outpatient or telephone/mail**	
Eligibility criteria	X						
Informed consent	X						
Baseline demographics and clinical data	X						
Randomization	X						
Surgical data		X					
Histopathology (lymph node count, R0-rate)		X					
Assessment of primary endpoint (CCI)			X	X	X		
Assessment of reoperations			X	X	X	X	X
Safety (SAE)			X	X	X	X	
Assessment of secondary, oesophagectomy-specific outcomes according to ECCG			X	X	X		
Length of hospital stay				X			
Pain at rest and during movement (NRS)			X				
Thoracic pain syndrome measured as pain in the chest at rest and while coughing (NRS)			X	X	X	X	X
Quality of recovery (QoR-15)	X		X				
Health-related quality of life (EORTC QLQ-C30 + OES-18)	X				X	X	X
Disease-free survival					X	X	X
Overall survival (including 90-day mortality)		X	X	X	X	X	X

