### Adverse event reporting and harms {22}

During the MICkey trial, adverse events are assessed as minor complications (Clavien-Dindo grade <3) within 30 days postoperative (primary endpoint).

Serious adverse events in the MICkey trial are defined and assessed as major postoperative complications Clavien-Dindo grades III–V within 90 days after the index operation. In addition, also intraoperative deaths and intraoperative conversions from minimally invasive to open surgery will be documented.

Since the MICkey trial is a clinical trial according to Medical Association’s professional code (Berufsordnung der Bundesärztekammer) § 15, no specific SAE management is required. However, a GCP-conform AE and SAE management is implemented. AE and SAEs will be collected via the primary and secondary endpoints directly in the EDC system.

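### Visit 7 may be held from POD 25 and visit 8 from POD 85, so scheduled collection of complications can end before the 30-day and 90-day endpoint periods close

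*Protocol article*

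**What the plan says.** All references are to the protocol article.

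- **Endpoint period.** The abstract fixes the period: "The primary endpoint will be overall postoperative morbidity assessed via the comprehensive complication index (CCI) within 30 days after surgery". Outcomes {12} defines the CCI over 30 days and leaves nothing out: "The score will be calculated comprising all complications within 30 days". The ECCG-specific secondary outcomes (pulmonary complications, anastomotic leak, conduit necrosis, delayed conduit emptying, chyle leak, recurrent nerve injury) are also defined over 30 days.
- **Safety endpoint.** Safety measures defines the SAE rate as "postoperative complication Clavien-Dindo grades III–V within 90 days after surgical intervention".
- **Visit schedule.** In Participant timeline {13}, the row beginning "Assessment of primary endpoint (CCI" and the ECCG row are marked at visits 3-5, 6 (discharge) and 7, and not afterwards. Visit 7 is set at POD 30 with a tolerance of five days either way. The SAE row continues to visit 8 and stops there; visit 8 is set at POD 90 with the same tolerance. Re-operations and survival are marked through visits 9/10.
- **Source of event data.** Adverse event reporting and harms {22} limits minor events to the primary endpoint period: "adverse events are assessed as minor complications (Clavien-Dindo grade <3) within 30 days postoperative (primary endpoint". It adds: "AE and SAEs will be collected via the primary and secondary endpoints directly in the EDC system". No separate stream for minor events is described.

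**The concern.** A visit 7 on POD 25-29 complies with the schedule, yet it is the last planned occasion for recording the CCI, and one to five days of the endpoint period are still to come. The tolerance acts in one direction only. A late visit does no harm, because events can be cut at day 30 by their date. An early visit can only lose events. The same asymmetry applies to SAEs at visit 8.

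Analysis cannot repair the loss. A CCI closed on POD 25 looks complete, so the multiple imputation planned in section {20c} would not treat it as missing. That section also plans no sensitivity analyses of the imputation. At stake is uniform follow-up for the primary endpoint and for the 30-day and 90-day secondary endpoints.

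**Working it through.** **1. Date arithmetic (Participant timeline {13}).**
- Visit 7: 30 − 5 = POD 25 to 30 + 5 = POD 35. Earliest case: POD 26-30 (5 of 30 days) follows the last scheduled CCI and ECCG assessment.
- Visit 8: 90 − 5 = POD 85 to 90 + 5 = POD 95. Earliest case: POD 86-90 (5 of 90 days) follows the last scheduled SAE assessment.

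**2. Which events lack a later scheduled collection?**

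| Event after an early visit | Later scheduled collection |
|---|---|
| Grade I-II or minor ECCG event, up to POD 30 | None |
| Grade III-IV, up to POD 30 | Visit 8, as SAE |
| Re-operation, up to POD 30 | Visit 8 and later |
| Death, up to POD 30 | Visit 8 and later, as SAE and in survival |
| Non-fatal SAE, not a re-operation, up to POD 90 | None |
| Death or re-operation, up to POD 90 | Visits 9/10 |

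Patients still in hospital are covered differently. Visit 6 is the discharge visit, has no fixed day and is marked for the CCI, so a stay beyond POD 30 is assessed after the period has closed. The exposed group is patients already discharged, seen early, with a new event between visit 7 and POD 30.

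**3. Number of patients (illustration).** The article gives neither a distribution of visit dates nor an event rate for POD 26-30, so both are assumptions.
- Patients with oesophagectomy: 152 × 0.90 = 136.8, about 137 (10% intraoperative drop-out, Sample size {14}).
- Visit 7 spread evenly over the 11 days POD 25-35: 5/11 = 45% fall before POD 30, and 137 × 5/11 ≈ 62 patients.
- Mean shortfall among these: (5 + 4 + 3 + 2 + 1)/5 = 3 days, that is 3/5 of the five-day gap.
- Assumed 2-5% of patients with a new complication on POD 26-30: 62 × 3/5 × 0.02 = 0.7 to 62 × 3/5 × 0.05 = 1.9 patients.
- Extremes for visit dates: none if every visit 7 is on or after POD 30; 137 × 0.02 = 2.7 to 137 × 0.05 = 6.9 patients if every visit 7 is on POD 25.

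These counts cover events of any grade and ignore the discharge visit. Only grade I-II and minor ECCG events lack a later collection, so the true loss is smaller.

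**4. Power.** The plan's own figures reproduce. A two-sided t-test with α = 0.05, difference 10, SD 20 and power 0.80 needs 63.77, rounded up to 64 per group. Exact power at 64 per group is 80.1%. Inflation for 15% drop-out: 64/0.85 = 75.3, rounded up to 76 per group, 152 in total.

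If the under-count removes a share f of the difference, the detectable difference is 10 × (1 − f). With SD 20 and 64 per group unchanged:

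| f | Difference | Power |
|---|---|---|
| 0 | 10.0 | 80.1% |
| 1% | 9.9 | 79.4% |
| 2% | 9.8 | 78.5% |
| 5% | 9.5 | 76.0% |
| 10% | 9.0 | 71.4% |

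Step 3 points to the low end of this range. The documents do not fix f.

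**The case against.** The strongest reply is that the definition governs, not the visit date. The CCI comprises all complications within 30 days, and the timeline lists contact times without calling visit 7 a data cut-off. A symmetric tolerance is ordinary scheduling language, and how an early visit is completed to day 30 may be settled in the full protocol or the eCRF instructions, which are not shown here.

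Much of this stands. The endpoint definition is not shortened and the abstract sentence is correct; the weakness is in ascertainment. A look-back rule may exist elsewhere. But the visit windows and the collection rows are fixed in this document. As written, they leave minor events after an early visit 7 with no planned contact at which to record them, and an analysis plan cannot recover events that were never collected.

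Two stronger readings are tempting and are not supported:

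- **Deaths on POD 26-30 drop out of the CCI.** A reader might infer this from the missing CCI mark at visit 8. But survival and grade V events are collected at visit 8, and the section on intercurrent events places death and re-operation inside the primary endpoint. What is missing is only a stated rule that such events are carried back. The rule matters because section {20a} runs the primary analysis once primary endpoint data are available for all patients, without saying whether it waits for visit 8.
- **The loss differs between arms.** A reader might infer this because treating staff are unblinded. But the same windows apply to both arms, and nothing in the article links visit dates to allocation.

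The 90-day part is the weaker one: deaths and re-operations are picked up at visits 9/10, and secondary endpoints are evaluated descriptively.

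**Conclusion.** The schedule and the endpoint periods do not match. The last planned CCI and ECCG assessment may precede POD 30, and the last planned SAE assessment may precede POD 90, by up to five days each. The gap is confined to new grade I-II or minor ECCG events after an early visit 7, and to non-fatal SAEs other than re-operations after an early visit 8. For more serious events on POD 26-30 the data will exist, but the rule placing them in the CCI is not stated.

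The expected effect is a small under-count in both arms. If both arms lose the same fraction, the difference shrinks by that fraction; a 1-2% loss would take power from 80.1% to 79.4-78.5%. That size rests on assumed visit dates and event rates. It does not threaten the trial's conclusion, and correcting it is a cheap improvement.

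**What to change.** 1. In Participant timeline {13}, set visit 7 to POD 30-35 and visit 8 to POD 90-95. Alternatively, keep the present windows and require a telephone contact on or after POD 30 or POD 90 whenever the visit was earlier.
2. In Outcomes {12}, state that the CCI counts every event dated up to POD 30, whenever it is recorded, including events first reported at visit 8. State also whether the primary analysis waits for those data.

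The cost is slightly less freedom to schedule visits 7 and 8. Telephone visits are already allowed for patients unable to attend (Sample size {14}; Plans to promote participant retention {18b}), so the second option adds a call only for patients seen early. The sample size stays at 128 evaluable and 152 randomized.

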**Discussion:**

The MICkey trial will address the yet unanswered question whether the total minimally invasive oesophagectomy (MIN-E) is superior to the HYBRID-E procedure regarding overall postoperative morbidity.

**Trial registration:**

DRKS00027927 U1111-1277-0214. Registered on 4th July 2022

**Supplementary Information:**

The online version contains supplementary material available at 10.1186/s13063-023-07134-1.

## Administrative information

Note: the numbers in curly brackets in this protocol refer to SPIRIT checklist item numbers. The order of the items has been modified to group similar items (see http://www.equator-network.org/reporting-guidelines/spirit-2013-statement-defining-standard-protocol-items-for-clinical-trials/).

## Introduction

### Background and rationale {6a}

Oesophageal cancer (EC) is the sixth leading cause of cancer death and the eleventh most common cancer worldwide [1]. Overall survival among patients with EC remains poor with an overall survival of 18%. The only curative treatment of EC is oesophageal resection, frequently in combination with other multimodal treatments. For resectable patients, the 3-year survival is around 50% [2, 3]. In Germany, 3500 resections of the oesophagus are performed each year [4]. Significant improvements in surgical practice and centralization in high-volume centres have reduced perioperative mortality after oesophagectomy to 5%. Yet, the risk for a major complication is as high as 50% [5–8] which leads to prolonged postoperative recovery, reduced health-related quality of life and increased costs [9]. Therefore, interventions that improve overall postoperative morbidity are urgently needed.

Due to the anatomical position of the oesophagus, a two-cavity oesophagectomy via abdominal and right thoracic approach (Ivor-Lewis procedure) and thoracic and abdominal lymphadenectomy is required for tumour resection. This can be either done via open surgery (with laparotomy and right thoracotomy) or via total minimally invasive oesophagectomy (MIN-E; either via “classical” minimally invasive laparoscopy and thoracoscopy; or via robotic-assisted minimally invasive oesophagectomy [RAMIE] or any combination of the two). Alternatively, a hybrid procedure (HYBRID-E) via laparoscopic/robotic abdominal surgery and open thoracic surgery is possible. Until recently, open oesophagectomy represented the standard procedure. However, over the last years, results from a number of randomized controlled trials (RCTs) have challenged this notion and have established MIN-E or HYBRID-E as new standard procedures for Ivor-Lewis oesophagectomy due to its reduced complication rates compared to open oesophagectomy.

Due to the lack of high-quality RCTs directly comparing HYBRID-E and MIN-E, it is unclear whether MIN-E represents an additional advantage over HYBRID-E in terms of postoperative morbidity. The available literature on MIN-E compared to HYBRID-E is heterogeneous with different surgical techniques and a high risk of bias due to the retrospective character of the analyses, small numbers of patients and historical cohorts [5, 7, 8, 10, 11]. On the one hand, a retrospective case series comparing MIN-E to a historic control group consisting of a patient population of open and HYBRID oesophagectomy revealed superiority for MIN-E regarding overall survival, perioperative mortality and severity of postoperative complications. This study exhibits a high risk of bias [12]. Another large retrospective comparative study with three groups (open versus MIN-E versus HYBRID-E) revealed improved survival in the MIN-E but not in the HYBRID-E group compared to the open procedure, again with a high risk of bias due to lack of adjustment for confounder variables [13]. A propensity score-matched comparison showed that MIN-E for EC reduces postoperative pain and pneumonia compared to HYBRID-E, but showed no difference in terms of postoperative surgical complications [14]. On the other hand, in a prospective comparative study including 315 patients, published as a congress abstract, a trend towards higher rates of overall complications and anastomotic leaks (without statistical significance) was reported for MIN-E compared to HYBRID-E [15]. In summary, data from a high-quality RCT comparing MIN-E versus HYBRID-E are lacking.

Therefore, according to the IDEAL framework, a multicentre RCT is indicated to test the comparative effectiveness of MIN-E vs. HYBRID-E (IDEAL stage 3; assessment) [16]. The MICkey trial will compare HYBRID-E vs. MINE-E in patients undergoing elective Ivor-Lewis oesophagectomy in respect to overall postoperative morbidity.

## Objectives {7}

The objective of the MICkey trial is to evaluate whether total minimally invasive Ivor-Lewis procedure (MIN-E, total minimally invasive abdominal-thoracic oesophagectomy) is superior to hybrid Ivor-Lewis procedure (HYBRID-E, minimally invasive abdominal surgery and open thoracic surgery) regarding overall postoperative morbidity measured via the comprehensive complication index [17, 18].

## Trial design {8}

MICkey is a multicentre, randomized controlled, patient-blinded superiority trial with two parallel study groups.

## Methods: participants, interventions and outcomes

### Study setting {9}

The trial will be performed by the Clinical Trials Network of the German Surgical Society (CHIR-*Net*, www.chir-net.de). To enrol the required number of patients in the planned recruitment period, eight trial sites with high expertise will participate. A list of study sites can be found in Supplement 1. Centres were chosen based on their expertise in oesophageal surgery. All centres must perform more than 26 oesophagectomies per year. Participating surgeons must have a lifetime experience of 40 MIN-E and/or 40 HYBRID-E.

### Eligibility criteria {10}

#### Inclusion and exclusion criteria for patients

All patients with a malignant tumour of the oesophagus or the oesophagogastric junction considered to be resectable with curative intent via oesophagectomy by means of an abdominal and right thoracic approach (Ivor-Lewis procedure) irrespective of neoadjuvant therapy are eligible for the study. All subjects must be suitable for the MIN-E and for the HYBRID-E procedure. Only adult patients (≥18 years of age) with the ability to understand character and individual consequences of the clinical trial will be included. All subjects must provide a written informed consent.

The preoperative exclusion criteria are defined as the presence of distant metastases, tumour localization above the azygos vein, history of right thoracotomy within the last 3 years, American Society of Anesthesiologists (ASA) grade >3 and advanced hepatic cirrhosis (Child B/C). Patients who participate in another intervention trial with interference of the intervention and/or primary outcome of the MICkey trial will be excluded as well as patients with an expected lack of compliance or language problems. Furthermore, two intraoperative exclusion criteria are defined: (a) intraoperative diagnosis of previously occult metastases that prohibit surgical resection according to current S3 guidelines [19] and (b) the tumour resection is technically impossible. For further handling of these cases (i.e., intraoperative exclusion of previously randomized patients), please refer to the section “Criteria for discontinuing or modifying allocated interventions {11b}”.

#### Eligibility criteria for trial sites and surgeons

The eligibility criterion for each participating trial site is the commitment to include ≥ 10 cases per year and can thus be regarded as major oesophageal cancer surgery centres [20]. This criterion is irrespective of the actual recruitment. Furthermore, all surgeons must have performed a minimum of 40 MIN-E or 40 HYBRID-E respectively to participate in the trial.

### Who will take informed consent? {26a}

All patients scheduled for an abdomino-thoracic oesophagectomy will be informed by an investigator, orally and written, of the aims of the study, the possible risks, the procedures, and possible hazards to which he/she will be exposed, and the mechanism of treatment allocation (randomization). The written informed consent form will be signed and personally dated by the patient according to the ICH guidelines on Good Clinical Practice.

### Additional consent provisions for collection and use of participant data and biological specimens {26b}

No biological samples will be collected during the trial.

## Interventions

### Explanation for the choice of comparators {6b}

Patients in both groups will receive oesophagectomy for their underlying tumour disease either via MIN-E or HYBRID-E. As pointed out in the “Introduction” section, both procedures have been shown to result in better outcomes than open oesophagectomy and can thus be regarded current standard of care. No high-level evidence directly compares the MIN-E and HYBRID-E directly. Therefore, a real clinical equipoise exists between the two comparators (see the “Introduction” section).

### Intervention description {11a}

#### Experimental and control intervention

In the experimental group, both the abdominal and thoracic phases of the elective oesophagectomy will be performed minimally invasively, i.e. as total minimally invasive oesophagectomy (MIN-E). MIN-E can be performed either via “classical” minimally invasive laparoscopy and thoracoscopy or via robotic-assisted minimally invasive oesophagectomy (RAMIE) or any combination of the two. A recent international consensus study has developed an operation manual for oesophagectomy [21]. The following steps are an adaptation of this consensus and serve as an operation recommendation for both the experimental and control interventions. Surgeons in the MICkey trial may deviate from this manual and should perform the procedure according to their local standard, i.e. according to the technique in which the operating surgeon has reached the plateau of her/his learning curve. In the following, the lymph node sections are named according to the Japan Esophageal Society and Japanese Gastric Cancer Association.

